## Abstract

Aim: to analyze the efficacy of an educational online intervention focused on lifestyle changes in reducing body weight from baseline to 6 months in the pre-diabetic population of 18–45 years old in Extremadura (Spain). Methods: a single-blind, multicenter randomized parallel-comparison trial with two intervention groups in a 1:1 ratio will be carried out. Participants will be randomly assigned to intervention A or B with 37 cases in each group according to inclusion criteria of being enrolled or working at Extremadura University, scoring >7 points on the Findrisc test and not having diagnosed diabetes mellitus or physical disabilities. Intervention-A group will have access to online information about healthy diet and exercise. Intervention-B group will have access to a six-session educational program regarding behavioral changes in diet and exercise habits. They will complete follow-up activities and have a personal trainer and motivation. The primary outcome will be identifying changes in body weight from baseline to 1 and 6 months and between groups. The secondary outcomes will be accomplishing regular physical activity (>30 min/day or >4 h/week), decreasing sugary food intake or avoiding it altogether, increasing vegetable/fruit intake and lowering HbA1c levels to non-diabetic status when necessary.

## 1. Introduction

Diabetes mellitus (DM) represents one of the most prioritizing health issues due to the economic burden and social and sanitary impact [1]. It has been denominated as the ‘21st century epidemic’ as a result of the prevalence surge and the recurrent appearance of both chronic and acute complications associated with it [2,3]. Diabetes mellitus prevalence has been estimated at 9.3% worldwide and 10.5% in Spain among the 20–79 aged population by the International Diabetes Federation. Nowadays, 463 million people in the world are diagnosed with DM, 3.6 million in Spain. These data make Spain the fifth European country in the ranking of highest DM prevalence. By 2045, IDF estimates that there will have been an increase in the DM incidence of 700.2 million people in the world and 5 million in Spain [4].

Type-2 diabetes mellitus (T2DM) embodies 90–95% of all diabetes diagnoses in developed countries. On this account, modifiable factors such as obesity and unhealthy lifestyles are associated with the increase in type-2 diabetes, triggering precocious T2DM development among children and adolescents [1,5].

Diabetes screenings are performed in the presence of overweight/obesity or other risk factors such as family DM history, race (African, African American, Hispanic, Native Americans, Asians, and Pacific islanders), cardiovascular alterations, hypertension, polycystic ovary, dyslipidemias, sedentary lifestyle, HIV or being older than 45 years old [5,6,7]. Notwithstanding this fact, undiagnosed diabetes rates are 40.7%, thus being more prone to developing complications [4].

T2DM management focuses not only on diagnosis, but the literature shows that changes in the lifestyle can prevent its advance, being also cost-effective [7,8,9,10,11,12]. Consequently, early screening interventions to detect at-risk populations are paramount, especially in those younger than 45 years old where the incidence is increasing and individuals usually are not a target in the healthcare screening process [13].

The T2DM diagnosis gold standard is the oral glucose tolerance test (OGTT) which contains drawbacks of being a complex, burdensome and expensive test [11,14,15]. Nonetheless, the Finnish Diabetes Risk Score (FINDRISC) has been proven as a cost-effective alternative that allows clinicians to predict T2DM risks and screen for prediabetes status. It assesses age, body mass index (BMI), waist circumference, hypertension history, regular physical activity, daily consumption of fruits and vegetables, and DM family history [7,9,10,11]. Several large studies in Europe have employed FINDRISC as an efficient tool to screen diabetes such as the German National Diabetes Prevention Programme [16], the Diabetes in Europe: Prevention using Lifestyle, Physical Activity and Nutrition intervention (DEPLAN) [17] or the European Guideline and Training Standards for Diabetes Prevention (IMAGE) [18].

The American Diabetes Association (ADA) indicates that changes toward a healthier diet and an active lifestyle—avoiding overweight—throughout educational interventions have been proven effective, with a positive impact on T2DM prevention [6]. In addition, several randomized trials testing prevention programs focused on education have also been effective. For instance, the Diabetes Prevention Program (DPP) improved anthropometric and certain metabolic outcomes, reducing by 58% the T2DM incidence in 3 years [8]. In the Finnish Diabetes Prevention Study, T2DM incidence was lowered by 43% after 7 years [19]. The Da Quin study reduced the T2DM incidence by 39% after 30 years [20]. Finally, the metanalysis carried out by Renders et al. analyzed 41 studies, concluding that educational interventions have a positive effect on reducing T2DM [21].

Endpoint variation is shown in educational-centered studies by either focusing on changes in HbA1c values, diet, or body weight. Notwithstanding that fact, effectiveness is shown [22,23,24,25]. However, studies focused on younger populations are lacking, especially among 18–45 years old. Furthermore, the COVID-19 pandemic rescinded all health group-education interventions or activities and hindered individual education as well, being historically scarce and underdeveloped [26]. However, new technologies have proven their efficacy as an educational tool in DM, being a new resource to exploit in order to understand which educational interventions are the most efficient [27,28,29].

The study hypothesis is that online educational intervention focused on lifestyle changes is effective in reducing body weight when engaging activities are encouraged and present throughout the first weeks of behavioral modifications.

The aim of the study is to analyze the efficacy of an online educational intervention focused on lifestyle changes in reducing body weight from baseline to 1 and 6 months in the pre-diabetic population of 18–45 years old in Extremadura (Spain).

## 2. Materials and Methods

### 2.1. Study Design and Settings

The study is a single-blind, multicenter randomized parallel-comparison trial with two intervention groups in a 1:1 ratio. Participants were blinded to the allocated group, but researchers performing the intervention were not.

The trial registration code is 10.17605/OSF.IO/4D8FJ and was designed so that it can be reported according to the SPIRIT 2013 statement [30]. The study will be carried out across three centers of the University of Extremadura (UEx).

### 2.2. Participants: Eligibility, Recruitment, and Allocation

Participants were eligible for this trial when in accordance with the following selection criteria:

As inclusion criteria: ages 18–45, FINDRISC screening result >7 points, being enrolled or working at the University of Extremadura. As exclusion criteria: HbA1c compatible with type 2 diabetes, diabetes diagnosis, mobility disability and/or comorbidities incompatible with moderate exercise. 

### 2.3. Sample Size

The primary outcome was body weight change at 1 and 6 months. The power calculation assumed a 14 kg SD in baseline weight and a 0.9 correlation between baseline and 6-month weight [31]. As such, a sample size of 74 (37 per group) was required to give the trial 80% power to detect a 4 kg difference in mean weight change between groups at 6 months (*p* < 0.05, two-sided test).

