#### 2.8.3. Criteria for Discontinuation of Participation in the Study or of the Study

If a participant withdraws consent for participation in the study.If their physician determines that the continuation of the intervention is not preferable for an individual patient. At the moment, there is no reason that can be used to exclude a patient from the trial apart from the aforementioned exclusion criteria, which might minimize bias affecting the results of the study.If the study protocol cannot be followed.

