### 2.10. Ethics and Dissemination

The study is implemented in accordance with the Declaration of Helsinki and the ethical guidelines for medical research covering humans. This study has been approved by the Ethical Committee of Extremadura University (No.165//2021). No information identifying specific patients is stored alongside study data. Only the authors will have access to the final trial dataset. It is considered that harm to the patient will be rare because the examinations performed will be those undertaken in the usual medical examination. However, participants will freely exit the study if they want to.

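### The 74 participants are the number needed for analysis but are used as the number randomised, so 80% power requires every participant to be weighed at 6 months; section 2.8.3 also links stopping the intervention to leaving the study

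*Protocol article*

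**What the plan says.** Section 2.3 (Sample Size) assumes a baseline SD of 14 kg and a correlation of 0.9 between baseline and 6-month weight. It concludes that "a sample size of 74 (37 per group) was required to give the trial 80% power". The target is a gap of 4 kg between the arms in mean change by month 6, with the test at p "< 0.05, two-sided test". It mentions no loss to follow-up.

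The abstract takes the same figure as the number to be allocated: "Participants will be randomly assigned to intervention A or B with 37 cases in each group".

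Two places foresee departures. Section 2.10 says that "participants will freely exit the study if they want to". Section 2.8.3, whose heading concerns discontinuing participation in the study or the study itself, lists withdrawal of consent and two further criteria: "If their physician determines that the continuation of the intervention is not preferable for an individual patient" and "If the study protocol cannot be followed". Section 2.6 expects synchronous sessions to help retention and complete follow-up, but gives no rate.

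**The concern.** A sample size formula returns the number of participants whose outcome enters the analysis. If that number is also the number randomised, the stated power assumes that nobody is lost. Here the primary outcome is read up to 6 months after baseline, in students and staff who may leave at will, and the article itself lists ways of leaving. A later analysis plan cannot restore participants who were never randomised, so this is not a detail that can wait for that document.

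The second issue is how people leave. Section 2.8.3 places a decision about the intervention under criteria for ending participation in the study. Read literally, a person whose physician advises against continuing the intervention leaves the trial, and the 6-month weight may go with them. The arms differ greatly in what there is to stop: arm B has six 2-hour sessions, a food diary, a fitness wristband and a personal trainer, while arm A has online material and appointment reminders. If stopping differs by arm and is related to weight, the comparison of those who remain is no longer fully protected by randomisation.

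**Working it through.** **Inputs.** From section 2.3: SD 14 kg, correlation 0.9, difference 4 kg, two-sided alpha 0.05, power 80%. From section 2.1: allocation 1:1. From the abstract: 37 randomised per group. Loss rate: not given, so 5% to 30%, equal in both arms, is assumed.

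**Step 1: reproduce the plan's figure.**
- Baseline-adjusted variance: 14² × (1 − 0.9²) = 196 × 0.19 = 37.24, so SD = 6.10 kg.
- n per group = 2 × (1.960 + 0.842)² × 37.24 / 4² = 2 × 7.849 × 37.24 / 16 = 36.5, rounded up to 37, total 74.

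This matches the stated 74 exactly. An unadjusted change score would have variance 196 × 2 × (1 − 0.9) = 39.2 and need 2 × 7.849 × 39.2 / 16 = 38.5, that is 39 per group (78). The plan's figure is therefore the baseline-adjusted one, and no loss allowance is hidden in it.

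**Step 2: how much slack is there?** Power = Φ(4 / (6.10 × √(2/n)) − 1.960).
- n = 37: Φ(2.820 − 1.960) = 80.5%.
- n = 36: Φ(2.781 − 1.960) = 79.4%.

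One lost weight per arm takes power just below 80%. With the noncentral t distribution, 37 per group gives 79.4% and 38 would be needed.

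**Step 3: power with 74 randomised and assumed equal loss d.** Analysed per arm = 37 × (1 − d), left unrounded. The third column uses the method that reproduces 74. The detectable difference at 80% power is 2.802 × 6.10 × √(2/n), also by the normal approximation.

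| Assumed loss | Analysed per arm | Power, normal | Power, noncentral t | Detectable difference |
|---|---|---|---|---|
| 0% | 37 | 80.5% | 79.4% | 3.97 kg |
| 5% | 35.15 | 78.5% | 77.3% | 4.08 kg |
| 10% | 33.3 | 76.3% | 75.0% | 4.19 kg |
| 20% | 29.6 | 71.3% | 69.8% | 4.44 kg |
| 30% | 25.9 | 65.5% | 63.8% | 4.75 kg |

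**Step 4: number to randomise if 37 analysed per arm is to be kept.** 37 / (1 − d), rounded up: 39 per arm (78) at 5%, 42 (84) at 10%, 47 (94) at 20%, 53 (106) at 30%.

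**Step 5: the discontinuation wording.** The heading of section 2.8.3 is about participation in the study. The physician criterion beneath it is about continuing the intervention. No section says that a person who stops the intervention will still be weighed at 1 and 6 months. The criterion on a protocol that cannot be followed may refer to one participant or to the whole study; the text does not settle which.

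**The case against.** The strongest reply is that section 2.8.3 can be read more kindly. Between its criteria it says that, beyond the stated exclusion criteria, there is at present no ground for excluding a patient, and it links this to minimising bias. That suggests an intent to keep people in. Nowhere does the article say that 6-month weights will not be collected after the intervention is stopped, and a condensed article commonly leaves data collection after discontinuation and the analysis set to fuller documents. This has force: the loss of weights is a possible consequence of the wording, not a stated rule. What remains is that the text places a decision about the intervention under the criteria for ending study participation, and that pairing should be undone.

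A reader might go further and infer that removals will fall mainly on poorly adherent people in arm B, leaving a selected group and inflating its advantage. The documents do not support this. No criterion removes someone who merely skips sessions or does not keep the diary. Arm B also receives a trainer, regular feedback and synchronous contact meant to support adherence and retention, while section 2.6 says that arm A will not be encouraged or motivated by the researchers, so loss could equally be higher in arm A. Any percentage for the inflation would have to assume that all non-adherers are removed, that they gain nothing and that arm A loses nobody. None of these is in the article.

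It is also fair to say that the power loss is small if retention is good: about 2 points at 5% loss and 4 at 10%. That limits the size of the point but does not make 80% the right figure for 74 randomised.

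**Conclusion.** The point holds in two parts of unequal strength.

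The power part is firm. The arithmetic in section 2.3 is correct under baseline adjustment, but its result is the number to be analysed and the abstract uses it as the number randomised. How far power falls depends on a loss rate that the documents do not give. Over 5% to 30% equal loss, the shortfall against 80.5% runs from 2 to 15 points.

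The discontinuation part is a risk created by wording. Linking a physician's decision about the intervention to the end of study participation may cost 6-month weights, and may bias the comparison if such stopping differs by arm. Neither the direction nor the size of any bias can be derived from the article. Both parts should be corrected; neither invalidates the design.

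**What to change.** 1. In section 2.3, state that 80% power applies to 37 participants analysed per arm, and give the power with 74 randomised over an assumed range of loss (78.5%, 76.3%, 71.3% and 65.5% at 5%, 10%, 20% and 30%, by the method that gives 74). This makes the shortfall visible but does not remove it. If the sponsor prefers to keep 37 analysed per arm, step 4 of the working gives the numbers to randomise.
2. In section 2.8.3, separate stopping the intervention from leaving the study. Unless consent for follow-up is withdrawn, body weight is still collected at the scheduled 1- and 6-month visits. State that participants are analysed in the arm to which they were randomised, and make clear whether the criterion on a protocol that cannot be followed concerns a participant or the whole study.

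The clinical reasons for stopping stay as they are. The cost is a less favourable stated power, a few sentences of wording, and a few extra weigh-ins to chase at visits that are already planned.

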### 2.4. Recruitment

All participants from 18 to 45 years old will be reached through a standardized email sent to their university’s account where they will find an explanation of the project and the informed consent form with the possibility of either accepting to participate or declining any participation. Five researchers will reinforce the alumni’s participation with a visit during class hours and welcome to the project and explain it further. In the case of the university’s workforce, these five researchers will contact them during work hours in their workplace.

After two weeks’ notice, all volunteers who had signed the informed consent form will be summoned to follow the screening path which will be carried out using the Spanish version of the FINDRISC, which is a validated eight-item European questionnaire related to diabetes risk factors. This questionnaire has been validated in Spanish by the Pizarra Study in a Spanish population aged 18 to 65 years old. The results showed a 22.2% positive predictive value and 96% negative [11]. The study DE-PLAN—also developed in Spain—showed a 75.9% sensitivity and 52.3% T2DM diagnosis specificity and 65.8% prediabetes diagnosis specificity [32,33]. Furthermore, its utility has been demonstrated all over the world [16,32,33,34,35].

The FINDRISC screening will be carried out by six research nurses at the university centers. To those eligible participants with Findrisc results >7 points, researchers will ask them whether they have any mobility disability and/or comorbidities incompatible with moderate exercise in order to exclude those participants who do not meet the inclusion/exclusion criteria.

All suitable participants will be informed about their prediabetes status. Consequently, they will be offered to enter the study and will be given information and the calendar for the study.

As a result of participating in the study, additional clinical data will be collected such as capillary blood samples to measure HbA1c and fasting plasma glucose, lipid profile, BMI and blood pressure.

Furthermore, participants will fill in four questionnaires in the Spanish version regarding current exercise and diet preferences, and diabetes knowledge. To assess exercise, we will use the Rapid Assessment of Physical Activity questionnaire (RAPA) [36]. To assess participants’ current diet, we will use the Three-Factor Eating Questionnaire (Tfeq-Sp) [37], Yale Food Addiction (YFAS) [38] and Emotional Eater Questionnaire (EEQ) [39]. Finally, to assess diabetes knowledge, we will use the Diabetes Knowledge Questionnaire (DKQ-24) [40]. Socioeconomic data will also be collected.

The recruitment will be carried out first in the Cáceres UEx center, followed by the UEx center in Mérida and Badajoz. The researchers will be the same in all centers, and it will be executed from September 2022 to April 2024.

### 2.5. Allocation

Participants will be randomly allocated to either intervention A or intervention B group by one researcher using a randomization list. The participant timeline can be read in Figure 1.

### 2.6. Intervention

Both groups will be separately summoned to receive details about the intervention protocol in a welcome synchronous session at the university.

Participants allocated to the intervention-A group will have been provided access to information about healthy diet and exercise through the university’s online campus, to help them implement long-term changes in their diet and exercise habits using videos, recorded classes, and online information. A reminder of the following measurement appointment in one month will be sent and then for the 6 months final data collection. This intervention group will not be encouraged or motivated by the researchers but rather informed of their status and recommended to implement healthy diet and exercise habits.

Participants allocated to the intervention B group will have been provided with a six-session educational program mixing synchronous and asynchronous methodology concerning educational and behavioral changes regarding diet and exercise habits. All sessions will be carried out on the university’s online campus in one month so participants can promptly implement their exercise routines and diet changes through several proposed activities that they should complete. The first month of lifestyle treatment is a critical period for helping participants achieve weight loss according to the results of Miller et al. [41].

Participants will be assigned a personal trainer to make follow-ups and provide personal motivation. This activity will be held by two clinical nurse researchers who are trained in motivating patients. There will be constant feedback regarding the process and possible distractors via mail, telephone, or videoconference in order to surge adherence to the intervention.

Each session will have 2 h duration and pivot on three main issues: diet, exercise, and motivation, which according to Zhang et al. have been proven to be the central issues to work on [29]. Using synchronous methods will help promote participant retention and complete follow-up.

The first session, named “walking toward a healthy diet”, will be dedicated to identifying those fatty and sugary foods (both hidden and naturally present) and explaining strategies to avoid them by interchanging them for healthier options.

It will also help participants acknowledge sources of stress linked to binge eating and provide them with some strategies according to the scores in the questionnaires. Furthermore, participants will learn about type-2 diabetes through an educational video created by nurse researchers.

After this session, participants will begin to register their fruits and vegetables and high fat and sugar food intake in a diary. Furthermore, they will try to identify barriers and stressors to a healthy diet.

In the second session, named “give exercise the value that it has”, we will focus on explaining the benefits of exercising, showing participants easy ways of exercising, and how to improve exercise adherence using motivation.

After this session, participants will begin to implement strength and aerobic exercise in their routine and register it using fitness tracker wristbands.

Session three, named “barriers and stressors that block me from implementing a healthy diet”, will be a synchronous group session focused on those found barriers and stressors to maintaining a healthy diet and designing a plan to tackle them. After this session, participants will implement the plan and register any digression.

Session four, named “get up and get moving”, will help reinforce exercise habits and give participants the option to discuss any encountered limitations, their best exercise hours, and exercise planning. After this session, participants will further implement their exercise plan.

Session five, named “dealing with our surroundings I”, will be a synchronous group session focused on a real-life testimonial speech from a young diabetic person who will discuss what it feels like to deal with type-2-diabetes at a young age. A colloquial will be initiated after the speech for every participant to ask or discuss any issue. Additionally, participants will be asked to share a healthy picnic with friends or family and post photos on the online campus. Another option will be to post on the online campus a video of themselves preparing a healthy meal. The purposes will be overcoming negative social signals related to food and being able to make healthy decisions regarding “eating outside”.

Session six, named “dealing with our surroundings II”, will be an asynchronous session showing Spanish influencers who promote healthy diets and exercises. After the session, participants will share photos of themselves practicing any exercise.

After these sessions, participants will be able to contact the researchers via email, telephone, or videoconference when necessary.

